##### Neuromuscular function

2.6.2.2

Test of muscle strength is performed using three dynamometers: A custom build digital leg-press dynamometer, a custom build digital handgrip dynamometer, and an isokinetic dynamometer (Humac Norm, CSMi, Stoughton, MA). Prior to testing, all dynamometers will be calibrated. During all trials, participants are instructed to contract as hard and fast as possible whilst receiving verbal encouragement along with visual feedback to motivate participants to perform at maximal intensity.

In the leg-press dynamometer, isometric MVC is assessed unilaterally in a seated position with 15° knee flexion and 100° hip flexion. Participants are instructed to sit with their arms crossed over their chest. Three trials are performed with each leg or until no increase in maximum force is produced and the trial with the highest MVC is chosen for further analysis. In addition to leg-press MVC, force steadiness is also assessed during leg-press, which is a measure known to be related to motor function (e.g., walking) [84,85]. To investigate force steadiness participants are instructed to follow one-half of a sine curve wavelength by grading the force produced during leg-press. The half wavelength durantion is 20 s and peaks at 35% of MVC based on the average of leg-press MVC trials. The sine curve is displayed on a screen together with real-time display of force trace produced. Participants perform two force steadiness trials which are averaged.

Using a custom build handgrip dynamometer isometric MVC is assessed unilaterally with the participant seated in a chair without armrests, feet flat on the ground, arms along the torso, and holding the dynamometer in a neutral wrist position. The handgrip dynamometer is placed in the hand so that middle phalanx pressed the dynamometer into the palm of the hand. Three trials producing handgrip MVC are performed with each hand or until no increase in maximum force is produced. The trial with the highest MVC is chosen for further analysis.

In the isokinetic dynamometer MVC contractions of the weakest leg, determined from the leg-press test, is assessed. This includes knee extensors, knee flexors, plantar flexors, and dorsal flexors. Assessments are isometric contractions and isokinetic contractions at 60°/s and 180°/s. When assessing knee extension and flexion participants are seated upright with the hip in 85° flexion and the lateral epicondyle of the knee is aligned with the axis of rotation of the lever arm of the dynamometer. A Velcro strap placed 5 cm proximal to the medial malleolus secures the dynamometer arm to the leg of the participant. When assessing plantar flexion and dorsal flexion participants are seated upright with the hip in 50° flexion and the knee in 45° flexion. The bare foot is placed on a footplate, so the lateral malleolus of the ankle is aligned with the axis of rotation of the lever arm of the dynamometer, and then fixed using Velcro straps. For both knee and ankle assessments a shoulder and hip harness are used to fixate the participants, hence minimising extraneous body movement. Three trials are performed or until no increase in maximum force is produced for each condition. The trial with the highest MVC for each condition is chosen for further analysis. From this trial, RFD is also determined at 50 ms and 200 ms relative to the onset of contraction, defined as a torque increase of 2 standard deviations (SD) from baseline torque level at rest.

During the measurements of knee extension in the isokinetic dynamometer, the interpolated twitch technique (ITT) is also applied to determine voluntary activation (VA) of the quadriceps muscle [86,87]. Hereby, given a proxy measure of neural drive activating the quadriceps muscle. The ITT consist of an initial familiarization with electrical stimulation (direct current stimulator, model DS7A, Digitimer Ltd, UK) along with determination of the maximal individual stimulation current. The electric stimulation consists of doublet twitches (200-μs duration, 10-ms interstimulus delay) of the quadriceps muscle using two 5 × 10 cm electrodes (Valutrode Lite, Axelgaard, Denmark) positioned 15 cm above the basis of the patella and 15 cm below the anterior superior iliac crest. The ITT stimulation is applied at the force plateau of the MVC and immediately after the MVC at rest, resting twitch. To calculate VA the following equation is used:VA = 100 − ((MVC - Force at stim) * (Force at stim / MVC) / Resting twitch force) * 100

Hereby, adjusting for situations where the superimposed stimulation is not delivered exactly at peak MVC [88].

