### Outcomes

2.6

All outcomes will be assessed at week 0, 24, and 48. An overview of outcomes can be seen in Table 3.

**Table 3 tbl3:** Overview of test.

	Pre intervention test	Post intervention test	Follow-up test
Brain MRI			
MP2RAGE	x	x	x
T2 Space, dark fluid	x	x	x
DKI	x	x	x
Leg MRI			
Leg 2D Dixon	x	x	x
Muscle strength			
Bilateral leg press	x	x	x
Hand grip	x	x	x
Knee extension	x	x	x
Knee flexion	x	x	x
Plantar ankle flexion	x	x	x
Dorsal ankle flexion	x	x	x
Neural function			
ITT	x	x	x
EMG	x	x	x
Cognition			
SRT	x	x	x
SDMT	x	x	x
Clinical disability			
EDSS	x		
Physical function			
T25FWT	x	x	x
SSST	x	x	x
6MWT	x	x	x
9SSA	x	x	x
NHPT	x	x	x
1STS	x	x	x
5STS	x	x	x
Standing balance	x	x	x
Blood sample			
Neurodegenerative factors	x	x	x
Neurotrophic factors	x	x	x
Immunological factors	x	x	x
Bone metabolism	x	x	x
Body composition			
DXA	x	x	x
Physical activity			
Accelerometry	x	x	x
Questionnaires			
MSIS	x	x	x
MSWS	x	x	x
HADS	x	x	x
MFIS	x	x	x
EQ5D	x	x	x
FES-I	x	x	x
PSQI	x	x	x
ADL	x	x	x
BPI	x	x	x

Abbreviations: MP2RAGE: Magnetization Prepared 2 Rapid Acquisition Gradient Echo, DKI: Diffusion kurtosis imaging, T25FWT: Timed 25-foot walk test, SSST: Six spot step test, 6MWT: Six-minute walk test, 9SSA: Nine step stair accent, NHPT: Nine-hole peg test, 1STS: one time sit-to-stand test, 5STS: five time sit-to-stand test, SRT: Selective reminding test, SDMT: Symbol digit modality test, EDSS: Expanded disability status scale, DXA: Dual-energy X-ray absorptiometry MSIS: Multiple sclerosis impact scale, MSWS: Multiple sclerosis walking scale, MFIS: Modified fatigue impact scale, HADS: Hospital anxiety and depression scale, EQ-5D: Euro quality of life 5-dimension, FES-I: Falls efficacy scale-international, PSQI: Pittsburgh sleep quality index, ADL: Activities of daily living, BPI: Brief pain inventory.

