### Statistics

2.8

Characterization of the study sample across groups will be carried out using multiple baseline demographic and anthropometric variables (reported as number of observations, mean ± SD or median ± IQR, and proportions were appropriate). Data is checked for normality via visual inspection of histograms and quantile-quantile plots. In case of non-normality, appropriate data transformations will be performed. To investigate the effect of the 24 weeks PPT intervention and the 24 weeks follow-up period on the primary outcome (i.e., whole brain atrophy rate), a linear mixed model with repeated measures is used with group and time as fixed effects and participant id as random effects. The secondary outcomes will be analyzed analogous to the primary outcome. The analyses are performed following the intention-to-treat principle (i.e., all participant data are included, but without use of “last observation carried forward”) as the mixed model allows for missing value. In addition, a per-protocol analysis is performed based on adherence levels (only including participants that attend ≥80% of the planned PPT training sessions). An alpha level of 0.05 is used for all comparisons.

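### The printed voluntary-activation equation has no term for the force evoked by the superimposed doublet, so this one secondary outcome is wrong as written

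*Protocol article*

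**What the plan says.** In the protocol article, section 2.6.2.2 (Neuromuscular function), "the interpolated twitch technique (ITT) is also applied to determine voluntary activation (VA) of the quadriceps muscle", and the result is described as "given a proxy measure of neural drive activating the quadriceps muscle". On timing, "The ITT stimulation is applied at the force plateau of the MVC and immediately after the MVC at rest, resting twitch". VA is then set equal to 100 minus a product whose printed form ends "MVC - Force at stim) * (Force at stim / MVC) / Resting twitch force) * 100". None of the three symbols is defined. The next sentence gives the purpose of the formula: "adjusting for situations where the superimposed stimulation is not delivered exactly at peak MVC".

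ITT appears in Table 3 under neural function, next to EMG. Section 2.6 states that "All outcomes will be assessed at week 0, 24, and 48", and section 2.8 that "The secondary outcomes will be analyzed analogous to the primary outcome". VA is therefore a secondary outcome, measured at three visits and entered in the same mixed model as the primary outcome.

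**The concern.** The test gives two stimuli so that two evoked forces can be compared: the extra force during the maximal contraction and the twitch at rest. The equation should hold both, plus a factor for a stimulus given below peak. It holds the resting twitch and a factor that looks like the off-peak correction. Where the extra evoked force should stand, it has the difference between MVC and the force at the stimulus. If both are voluntary forces, that difference is only the distance by which the stimulus missed the peak.

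At stake is a mechanistic outcome. The Introduction attributes strength gains after resistance training mainly to improved neural drive, and VA is one of the trial's indicators of it. If the printed equation were used, VA would not measure activation at any of the three visits.

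**Working it through.** **Inputs.** The equation, the timing of the stimuli and the purpose of the correction come from section 2.6.2.2. The article gives no force values, so all forces below are assumptions in arbitrary units. The result at peak needs no assumed value.

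**Notation.** M = the quantity printed as MVC; F = Force at stim; R = resting twitch; S = peak force after the superimposed doublet.

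- Printed: VA = 100 − [(M − F) × (F/M) / R] × 100
- With a twitch term: VA = 100 − [(S − F) × (F/M) / R] × 100, where M is peak voluntary force and F is voluntary force at the stimulus

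**Target value.** For M = F = 100, S = 110, R = 40: 100 − (10 × 1 / 40) × 100 = 75%.

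**Reading 1: M is peak voluntary force, F is voluntary force at the stimulus.** This fits the sentence after the equation.

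- Stimulus at peak: F = M, the first bracket is 0, and VA = 100% for any S and any R.
- Stimulus at 95% of peak (M = 100, F = 95, R = 40): 100 − (5 × 0.95 / 40) × 100 = 88.1%. S does not enter, so a fully activated muscle with no evoked twitch also scores 88.1%.
- Same timing with R = 60: 100 − (5 × 0.95 / 60) × 100 = 92.1%. The score moves with the resting twitch although timing and activation are unchanged.

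**Reading 2: F is the evoked peak.** M = 100, F = 110, R = 40: 100 − (−10 × 1.1 / 40) × 100 = 127.5%. Values exceed 100%, and weaker activation scores higher.

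**Reading 3: M is the evoked peak, F is voluntary force at the stimulus.** M = 110, F = 100, R = 40: 100 − (10 × 100/110 / 40) × 100 = 77.3%. For larger forces, with the stimulus at peak voluntary force (150) and R = 60:

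| Superimposed twitch | Printed, reading 3 | With twitch term |
|---|---|---|
| 6 | 90.4% | 90% |
| 15 | 77.3% | 75% |
| 30 | 58.3% | 50% |

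For the last row: 100 − (30 × 150/180 / 60) × 100 = 58.3%, against 100 − (30/60) × 100 = 50%. A true rise from 50% to 75% (25 points) would appear as 58.3% to 77.3% (19 points). Peak voluntary force no longer appears in the equation, so F/M cannot correct for an off-peak stimulus.

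**Summary.** None of the three readings supplies both a superimposed-twitch term and the off-peak correction that the article describes.

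**The case against.** The strongest defence is reading 3. The symbols are undefined, the doublet is given during the maximal contraction, and the peak of that trace can include the evoked force. On that reading the equation does contain the twitch and misses the target by 2.3 points in the first example. This stands in part: the absence of a twitch term holds on the better-supported reading, not on every conceivable one. It is not a full rescue, because it conflicts with the article's account of the correction and understates large activation deficits.

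The article also cites methods sources for the technique and for the correction. They are not available here, and the laboratory may compute VA correctly, in which case this is a reporting error only. That stands. A display equation that lost subscripts when converted to text is possible, but the expression is complete and its parentheses balance.

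A reader might go further and infer three things that the article does not support:

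- *Any group difference in VA would be an artefact of trigger timing.* Even under reading 1 the value off peak also depends on the resting twitch, and nothing shows that the analysis uses the printed line.
- *VA is the trial's direct measure of neural drive.* The article calls it a proxy, and Table 3 lists EMG beside it.
- *The trial's main conclusion is at risk.* The primary outcome is whole brain atrophy rate, and the sample size rests on that alone.

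**Conclusion.** The equation is wrong as written for one secondary outcome. On the reading the article itself supports, it returns 100% at peak whatever the evoked force, where the assumed example calls for 75%. Off peak, it reflects stimulus timing and resting-twitch size. The result at peak is algebraic; the other figures rest on the assumed forces. The practical harm depends on whether the analysis script follows the printed line, which the article does not show. Severity is minor to moderate.

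**What to change.** Replace the equation with:

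VA = 100 − [(peak force after the superimposed doublet − voluntary force at the stimulus) × (voluntary force at the stimulus / peak voluntary MVC) / resting twitch force] × 100

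Define each of the four forces beneath it. Before VA is analysed, confirm that the script uses this form, and recompute any VA values obtained otherwise.

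The cost is one corrected line and a script check. Section 2.7 says digital data are stored, so if the force traces are among them, recalculation needs no new measurements.

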##### DXA

2.6.2.3

Using dual-energy X-ray absorptiometry (DXA) scan (GE Lunar iDXA, GE Healthcare, Madison, WI), body composition as well as bone mineral density are evaluated. Subjects are DXA scanned on the same time of the day (±1 h) across testing time points. The software package (enCORE software v16.0; GE Healthcare, Madison, WI) is used to determine bone mineral density and t-score, young white female reference population, at whole body, femoral neck, and lumbar spine level; in addition, body weight, fat mass, and fat-free mass is also determined using the same software. Routine quality control of the DXA scanner finds the coefficient of variance to be 0.26%.

##### Blood markers

2.6.2.4

Blood samples are drawn from an antecubital vein in a resting state. 41,5 ml of whole blood is drawn into three 8.5 mL Vacutainer SST™ II PET tube with clot activator and separating gel (BD, USA), one 8 mL vacutainer K2-EDTA (BD, USA), and two S-monovette K3-EDTA 4 mL (Sarstedt, Germany) with 8 μL protease inhibitor comprised of 1 μg/mL Aprotinin (Roche Diagnostics, Mannheim, Germany), 100 μg/mL mM Pefabloc® SC protector (Roche Diagnostics, Mannheim, Germany) and 0.5 μM KR-62436 hydrate (Sigma-Aldrich, St. Louis, Missouri, United States). After blood is dawn the serum tubes coagulate at room temperature for 30 min and is subsequently centrifuged at 1300 g for 10 min. The serum is then divided into Eppendorf tubes in 1 ml aliquots. EDTA tubes are kept on ice and centrifuged at 1300 g for 10 min at 4 °C immediately after the collection of blood samples. The plasma is then divided into Eppendorf tubes in 1 ml aliquots. Serum and plasma samples is stored at −80 °C until further analyses.

Samples analyses include biomarkers for neurodegenerative factors (neurofilament light chain [89] and glial fibrillary acidic protein [90]), neurotrophic factors (brain-derived neurotrophic factor [91,92] and insulin-like growth factor-1 [92]), immunological factors (interleukin-6, tumor necrosis factor alpha, C-reactive protein [93], and S100 [94]), and bone metabolism (propeptide of type 1 procollagen, beta-C-terminal telopeptide [95], sclerostin [96], 25 OH D-vitamin, calcium, phosphate, and parathyroid hormone [95,97]). Hereby allowing for exploring the effect of PPT on these relevant biomarkers for neurodegeneration, neurotrophy, immune system, and bone health.

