### Random allocation procedure

2.4

Randomisation to either the PPT group or the control group will be performed after baseline testing by the project coordinator in a 1:1 allocation ratio. Allocation is done by the sealed envelope principle.

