##### Physical activity

2.6.2.6

Physical activity levels in pwMS are lower than in matched HC [102,103]. Physical activity is in the present study objectively measured using an accelerometer (Axivity AX3, Axivity, Newcastle, UK) worn for seven consecutive days. The accelerometer is placed on the mid-anterior thigh of the weaker leg using self-adhesive tape (Fixomull Stretch, BSN Medical, Hamburg, Germany). Data is sampled at 100 Hz with a sensitivity of ±8G. The setup of the accelerometers and the downloading of raw data are done using OmGuiV.1.0.0.43 (Newcastle University, UK). Thigh-worn accelerometers provide more reliable and valid measurements of physical activity compared to other placements. Data analysis is performed using custom-built software (Propero by [name], Odense, Denmark) as previously described [104]. Additionally, minutes of sedentary, light intensity, moderate intensity, and vigorous intensity physical activities will be determined based on relevant cut-off levels of counts per minute.

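### Seasonal markers such as 25-OH vitamin D are compared 24 weeks apart with no calendar-date term, which can cost precision if starts are spread over the year

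*Protocol article*

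**What the plan says.** Section 2.6 (Outcomes) sets the schedule: "All outcomes will be assessed at week 0, 24, and 48". Section 2.6.2.4 (Blood markers) lists "25 OH D-vitamin, calcium, phosphate, and parathyroid hormone [95,97" among the bone-metabolism markers and gives the blood panel an exploratory purpose: "Hereby allowing for exploring the effect of PPT on these relevant biomarkers for neurodegeneration, neurotrophy, immune system, and bone health". Section 2.6.2.6 (Physical activity) adds an accelerometer "worn for seven consecutive days".

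Section 2.8 (Statistics) names the terms of the primary model: "a linear mixed model with repeated measures is used with group and time as fixed effects and participant id as random effects". It then carries this over: "The secondary outcomes will be analyzed analogous to the primary outcome". Calendar date, month and season do not appear in the model, in the allocation (section 2.4, "in a 1:1 allocation ratio") or in the visit timing. The one timing control stated concerns the hour, not the time of year, and applies to DXA only: "Subjects are DXA scanned on the same time of the day (±1 h) across testing time points".

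**The concern.** Two visits 168 days apart fall at nearly opposite points of an annual cycle. A fixed visit term removes only a swing that all participants share. If entry is staggered, someone who starts in summer and someone who starts in winter move in opposite directions between week 0 and week 24. That spread goes into the residual, although the date of each visit is known.

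Bone health is named in the secondary aim, and section 2.3 sizes the trial on the primary outcome only. These markers therefore have no stated power margin from which to absorb avoidable noise. What is at stake is the width of the interval for the week-24 group contrast in a marker that varies with season.

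**Working it through.** **Inputs from the article.** Visits at days 0, 168 and 336 (section 2.6). Model terms: group, time and participant (section 2.8). Difference 0.3204 + 0.0148 = 0.3352, SDs 0.5253 and 0.2698, alpha 0.05, power 0.8, dropout 16% (section 2.3).

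**Inputs assumed.** An annual cosine of amplitude A (peak to trough 2A); for vitamin D, A = 0, 5, 10 or 15 nmol/L and within-person SD 12 nmol/L. Between-person SD (20 nmol/L) cancels in a change. None of these values is in the documents.

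**1. The plan's own figure.** Pooled SD = √((0.5253² + 0.2698²)/2) = 0.4176. n = 2 × (1.960 + 0.842)² × 0.4176² / 0.3352², which rounds up to 25 per arm. 25/0.84 = 29.8, so 30 per arm. The stated size is reproduced, and 25 completers per arm is used below.

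**2. Share of the swing in one change.** Largest change over d days = 2A·sin(πd/365.25).
- Week 0 to 24: sin(π × 168/365.25) = 0.992, or 99% of peak to trough.
- Week 0 to 48: 0.249, or 25%.

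**3. Seasonal variance of the 24-week change.** With starts even over a year it is 2A²·sin²(π × 168/365.25) = 1.97A². For shorter enrolment windows, averaged over where the window falls in the year, it is 1.17A² (6 months), 0.37A² (3 months) and 0.04A² (1 month). The visit term takes up the rest.

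**4. Vitamin D, year-round starts, no date term.** Non-seasonal variance of a change = 2 × 12² = 288. SE of the contrast = √(2 × (288 + 1.97A²)/25).

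| A (nmol/L) | Variance of change | SE | Interval width vs A = 0 |
|---|---|---|---|
| 0 | 288 | 4.80 | 1.00 |
| 5 | 337 | 5.19 | 1.08 |
| 10 | 485 | 6.23 | 1.30 |
| 15 | 731 | 7.65 | 1.59 |

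**5. Effect of date terms.** In a simulated three-visit participant-level model with the sine and cosine of each assessment date, the variance of the week-24 contrast changed by about +3%, -12%, -39% and -60% for A = 0, 5, 10 and 15. A hand check that charges 3% for the two terms agrees: 1.03 × 288 = 296.6, and 296.6/337, 296.6/485 and 296.6/731 give reductions of 12%, 39% and 59%.

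**6. Short enrolment.** With a 3-month window the simulated gain was about 1 to 15%. It depends on where the window falls. The average seasonal variance of 0.37A² is 9/297 = 3%, 37/325 = 11% and 83/371 = 22% of the total for A = 5, 10 and 15, before the cost of the terms. The multiplier runs from 0.03 to 0.71 across calendar positions.

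**7. Free of units.** Let r be A divided by the non-seasonal SD of the change. Variance inflation is 1 + 1.97r². For r = 0.1, 0.25, 0.5, 0.75 and 1.0 the interval is 1.01, 1.06, 1.22, 1.45 and 1.72 times as wide. An effect with 80% power once season is removed has power 0.79, 0.75, 0.63, 0.49 and 0.37.

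**8. Bias and type I error.** 4,000 simulated change-score analyses at r = 0.5 gave a bias of -0.004 SD and a type I error of 0.0495. The mean SE fell from 0.343 to 0.288 with date terms.

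**The case against.** The strongest case is that nothing here is an error. Section 2.8 gives one general sentence for dozens of secondary outcomes, and a fuller analysis plan could add covariates for single markers. The article does not say that any of these markers is seasonal, nor when participants enrol. The amplitudes are assumed, the blood panel is exploratory, and no power is claimed for it.

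Much of this stands. The size of the loss cannot be taken from the documents, and it may be negligible: a weakly seasonal marker (r = 0.1) loses 1% in interval width, and a 1-month enrolment window loses almost nothing. Figures are worked only for vitamin D; PTH, bone-turnover markers and accelerometry may behave differently. Four recruiting clinics and a single scanner make staggered entry plausible, but do not establish it. What does not stand is that the article is silent. It names the model's terms and extends that model to all secondary outcomes, so the date terms are an alternative to a stated method.

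Two stronger readings are tempting. The first is that a chance imbalance in start dates could pass for a training effect. Such imbalance is ordinary sampling error, already covered by alpha, and is not a separate harm. The second is that season biases the comparison. Randomised arms share the same seasons in expectation, so the group contrast is not biased. Season could shift a within-group change if starts cluster, but that is not the randomised comparison.

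One limit: the type I error was checked on change scores. It carries over to the mixed model if the standard error reflects the actual variance of the week 0 to 24 change. The article does not give the covariance structure, so no claim of excess false positives can rest on it.

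**Conclusion.** The point holds as a minor one about precision. The planned spacing captures almost the whole annual swing, and the stated model has no term that can remove it when start dates differ. Three assumptions carry the size: the marker is seasonal, its amplitude is in the range shown, and enrolment is spread over the year. If all three hold for vitamin D, the variance of the week-24 contrast is reducible by about 12% to 60%. If enrolment is short or seasonality weak, there is little to gain, and with no seasonality the date terms cost a little. It would be wrong to infer that the vitamin D or activity results will be invalid: the contrast stays unbiased, with correct type I error where that was checked. The primary outcome and the 30 per group are untouched.

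**What to change.** Add one sentence to section 2.8: the models for 25-OH vitamin D, and for PTH, bone-turnover markers and accelerometry to the extent that they are taken to be seasonal, include the sine and cosine of the calendar date of each assessment. The markers should be chosen before the data are compared by arm.

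The cost is 2 degrees of freedom per model and about 2 to 4% of variance for a marker that proves not to be seasonal. Assessment dates are known for every visit, so nothing changes in visits, randomisation or sample size.
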